#### Direct questions about religion

Building on previous work on the development of religious and ethnic identity [e.g., 61, 79–82], we include a set of questions designed to directly assess children’s explicit understanding of religion and their own religious identity. This is the final task in the Child Protocol; see Fig 2.

*Task design and procedure*. The task begins with the researcher saying, “The last thing I want to do is ask you a few questions about religion. I might use some words that you don’t know, and if that happens that’s totally okay, just let me know and we’ll skip that one. I might also ask you some questions that seem really silly or obvious to you, or I might even ask you the same thing a few different times—that’s because I’m talking to really little kids too and I need to ask it a few different ways.” The child is then presented with a set of questions in a fixed order, proceeding roughly from most open-ended and general to most close-ended and specific.

First, the researcher asks two open-ended questions about religion in general: (1) “When I say the word ‘religion,’ what do you think of? Can you explain what ‘religion’ means?”; and (2) “There are lots of different religions in the world. Can you tell me all the religions you’ve heard of?”

Then, the researcher asks an open-ended question about the child’s family’s religious identity. In some cases, this question is phrased as, “What about your family: Does your family belong to a certain religion?”; in other cases, the question is instead phrased as, “Does your family believe in a certain religion?” Researchers are allowed to ask both questions if they deem it appropriate, and these judgments are generally made in real time on a case-by-case basis. If the child indicates that their family does belong to or believe in a religion, the researcher follows up with the question, “Which religion?” If the child indicates that their family does not belong to or believe in a religion, the researcher follows up with the question, “Do you mean they don’t belong to a religion at all, or do you mean you don’t know which religion?” If at any point the child indicates that they are not sure how to answer the question, the researcher can choose to ask a pair of additional follow-up questions: “What does your family believe in? Does your family ever go to church, or synagogue, or temple, or mosque or anything like that?”

Regardless of children’s responses, the researcher then proceeds to ask two close-ended questions about the child’s religious identity. Both questions use the same format: “Are you [five or more specific religious groups, presented in a random order], or something else, or none of these?” In the first question, the specific religious groups are all superordinate-level religious groups: Children in all samples hear options corresponding to five of the major world religions (“Buddhist,” “Christian,” “Hindu,” “Jewish,” and “Muslim”); depending on the groups present in the local setting, some children also hear additional superordinate-level religious groups (e.g., “Sikh,” “Druze,” “Taoist”). In the second question, the specific religious groups are all subordinate-level religious groups (e.g., denominations or sects) and are selected to include roughly 5–8 locally salient groups (e.g., “Shia,” “Sunni,” “Protestant,” “Catholic”). Research teams working with more than one religious group within a single geographical location are encouraged to include the same response options for all religious groups. Finally, the child is asked, “Is there anything else you want me to know about you and your family?”

In the US samples, this task is estimated to take 2 to 4 minutes across the age range.

*Adaptation for US samples*. Children in all US samples are administered the same adaptation of this task. In the first close-ended question, the superordinate-level groups provided as response options are: “Buddhist,” “Christian,” “Hindu,” “Jewish,” and “Muslim,” with no additional sample-specific options; these are presented in a random order, followed by three additional options presented in a fixed order: “Something else,” “I don’t know,” and “None of these things.” In the second close-ended question, the subordinate-level groups provided as response options are “Catholic,” “Protestant,” “a member of the Church of Jesus Christ,” “Reform,” “Orthodox,” “Sunni,” and “Shia”; these are also presented in a random order, followed by “Something else,” “I don’t know,” and “None of these things,” which are presented in a fixed order.

*Parallel tasks with parents/caregivers*. There is no directly parallel task for parents/caregivers, although parents/caregivers are asked to provide a range of demographic information about themselves and their families; see “Parent Survey,” below.

*Planned analyses*. Analyses of the open-ended questions included in this task (e.g., “When I say the word ‘religion,’ what do you think of? Can you explain what ‘religion’ means?”) will be qualitative and exploratory in nature and are not described in this manuscript.

For the two close-ended questions about religious group membership, we hypothesize that children who are themselves members of a religious group will be more likely to select their own religious group than other religious groups, both when presented with a range of “superordinate” religious groups and when presented with a range of “subordinate” religious groups [see, e.g., 80]. To test this hypothesis, for each question we will examine the distribution of correct vs. incorrect responses, relative to what we would expect by chance (given the variable number of options presented to children in a given sample).

Developmentally, we hypothesize that children’s tendency to correctly self-identify will increase with age [see 61, 79, 81–83], both when presented with a range of “superordinate” religious groups and when presented with a range of “subordinate” religious groups. To test this hypothesis, for each question we will examine the main effect of participant age (4–10 years) on the likelihood of correct responses.

Beyond these predictions, we plan to conduct within-subjects comparisons of the two questions (about superordinate vs. subordinate group membership); to compare responses across samples from different cultural-religious groups; to explore relationships between children’s responses in this task and information provided in the Parent Survey; and to examine relationships between this and other tasks included in the Child Protocol.

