When a parent/caregiver indicates that a child is being raised in *multiple* religious traditions, the child is shown the protocol corresponding to the religion with which the parent/caregiver says the child is most familiar, and these children are included in the sample for that religious group. Roughly halfway through data collection, we will assess how many mixed-faith children have been included in each cultural-religious group, and whether their responses diverge substantially from other participants. If so, we plan to replace these participants with new participants from families who report the child being raised solely or primarily in that religious tradition.

When a parent/caregiver indicates a child is religiously unaffiliated, the child is given the protocol version associated with the religious tradition most familiar to the child. If the parent/caregiver says that the child is not familiar with any religion and there are no religions mentioned in any other part of the Family Interest Form, the child is given the Protestant protocol; this reflects our understanding of Protestant Christianity as a pervasive cultural-religious force across US history, and the most common religious affiliation in the US through the present day [47].

In all cases–for religious children and for unaffiliated children–the parent/caregiver is given the version of the Parent Survey that matches the version of the protocol that the child has been given, regardless of the parent/caregiver’s own religious affiliation and familiarity with religion. We tell families that if there is one parent/caregiver whose religious affiliation (or familiarity with a specific religion) is more similar to the child’s, we would prefer that individual to complete the Parent Survey and Caregiver-Child Conversation.

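### Self-identification is tested against chance from the option count, which rules out only uniform guessing; in the US Christian samples a default to 'Christian' would pass as self-identification

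*Protocol article*

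**What the plan says.** The Protocol article, section Direct questions about religion (Planned analyses), states a directional hypothesis: "children who are themselves members of a religious group will be more likely to select their own religious group than other religious groups". This is to hold for the superordinate and the subordinate list. For each question the test is stated thus: "examine the distribution of correct vs. incorrect responses, relative to what we would expect by chance (given the variable number of options presented". The option count meant is the one used at the child's own site. The paragraph that follows treats a correct answer as correct self-identification and tests whether it rises with age.

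Under Adaptation for US samples, "Children in all US samples are administered the same adaptation of this task". The first question names five groups (Buddhist, Christian, Hindu, Jewish, Muslim). On how the list is built, the article reads: "with no additional sample-specific options; these are presented in a random order, followed by three additional options presented in a fixed order". The three non-group answers are Something else, I don't know and None of these things. The second names seven (Catholic, Protestant, a member of the Church of Jesus Christ, Reform, Orthodox, Sunni, Shia) and adds the same three.

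The section Eligibility, inclusion, and exclusion criteria (US samples) explains why a child with no familiar religion gets the Protestant version. It describes Protestant Christianity as pervasive in US history and as "the most common religious affiliation in the US through the present day".

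**The concern.** Rejecting an option-count null shows that answers are not spread evenly. It does not show that the answer depends on which group the child belongs to, and that dependence is what self-identification means. The test also falls short of the hypothesis as worded. Against 1/8 with 75 children, 16 correct answers are enough to pass, even if another single label was chosen by more than 16 children.

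The gap matters most in the Protestant, Catholic and Latter-day Saints samples, where 'Christian' is the correct first-question answer. If children who do not know their religion lean towards the commonest word, all three samples can show above-chance self-identification with no self-knowledge in any of them. This is a named Research Question 2 result, and differences between groups in percent correct would carry the same distortion.

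The size of chance is also left open. Depending on whether the three non-group answers count as options, it is 1/5 or 1/8 on the first question and 1/7 or 1/10 on the second.

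**Working it through.** The plan gives no alpha, power or numeric chance level for this test, so there is no figure of its own to reproduce.

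**Inputs from the article.** n = 75 (minimum) or 100 (maximum) per US sample, from Sample size (US samples). First question: 5 named labels, or 5 + 3 = 8 options. Second question: 7 named labels, or 7 + 3 = 10 options.

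**Assumptions, not in the article.** Exact binomial test, upper tail 2.5%. Children have no self-knowledge but choose 'Christian' at rate d, with d from 0.25 to 0.40.

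**Step 1: pass mark.** Take the smallest r with P(X ≥ r | n, p0) ≤ 0.025.
- n = 75, p0 = 1/8: r = 16 (actual level 0.022).
- n = 75, p0 = 1/5: r = 23 (actual level 0.019).

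**Step 2: probability of passing with no self-knowledge.** This is P(X ≥ r | n, d), first question, one Christian sample, n = 75.

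| Default rate d | Null 1/8 | Null 1/5 |
|---|---|---|
| 0.25 | 0.81 | 0.16 |
| 0.30 | 0.96 | 0.49 |
| 0.40 | >0.99 | 0.96 |

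With n = 100 and d = 0.30 the figures are 0.99 and 0.62. A larger sample makes the false pass more likely.

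**Step 3: effect of the unstated denominator.** At d = 0.25 and n = 75, the choice between 1/5 and 1/8 alone moves the pass probability from 0.16 to 0.81.

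**Step 4: pooling does not remove it.** Take five equal affiliated samples, every child choosing 'Christian' at 0.50 and the rest spread evenly over the other seven options. Expected percent correct is 0.6 × 0.50 + 0.4 × 0.50/7 = 0.329, above both nulls. In the Jewish or Muslim sample alone the same behaviour gives 0.50/7 = 0.071, below both. At d = 0.30 the pooled figure is 0.6 × 0.30 + 0.4 × 0.70/7 = 0.22, so at lower default rates the pooled result depends heavily on the denominator.

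**Step 5: comparison with non-members.** If members and non-members choose the label equally often (0.50 and 0.50), a two-proportion comparison rejects in the favourable direction at its nominal 2.5%. For 0.70 against 0.50, power is 0.71 with 75 per sample and 0.83 with 100.

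**Step 6: limit of that comparison.** Suppose 75 Christian children have no self-knowledge and a 0.40 default. The comparators are 150 Jewish and Muslim children, who never say 'Christian' if they know their own group and otherwise share the default.
- Half know: comparator rate 0.40 × 0.5 = 0.20. The comparison rejects about 88% of the time (normal approximation).
- 30% know: comparator rate 0.40 × 0.7 = 0.28. It rejects about 45% of the time.

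A simple member versus non-member contrast therefore does not prove self-knowledge within the Christian sample.

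**The case against.** **The default rate is not documented.** This stands. The remark about Protestant Christianity explains which protocol version a child receives, not how children answer a question about themselves. In the Catholic and Latter-day Saints versions, the group labels used in earlier tasks are Catholic or member of the Church of Jesus Christ, contrasted with Muslim, so those tables do not supply 'Christian' as a group label. Jewish and Muslim children hear their own first-question label repeatedly, which could favour them. The figures above show how exposed the test is; they do not predict what will happen.

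**Self-knowledge in Jewish and Muslim samples would be missed.** A reader might infer this, but it rests on assumed rates and on the denominator. If 15% know and 5% of the rest pick the right label, percent correct is 0.15 + 0.85 × 0.05 = 0.1925. At n = 75 that rejects about 1% of the time against 1/5, but about 37% against 1/8.

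**Some children have no correct option.** A reader might infer this too. Every affiliated US sample has a named first-question option, and Something else is offered on both questions. Only a narrower statement holds: on the second question, Jewish children have Reform and Orthodox, and Muslim children Sunni and Shia, as named labels, while eligibility is by religion. Some may have no named label, and the article does not say how Something else is scored.

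**Other analyses soften the problem.** In part. The age test does not use the chance reference, an open question on the family's religion comes first, cross-sample comparisons are planned, and the protocol calls itself largely exploratory. None of these replaces the test attached to this hypothesis, and the cross-sample comparison is unspecified.

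**The plan must work at every site.** This stands. Some sites study one group and have no local non-members, so the option-count reference keeps a place there.

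**Conclusion.** The concern holds for the US samples and chiefly for the first question. The article itself sets a reference that tests only uniform guessing, so a shared preference for 'Christian' would pass as correct self-identification in three of five affiliated samples. Under the stated assumptions (no self-knowledge, default rate 25% to 40%, n = 75, one-sided 2.5%), the false pass occurs 81% to over 99% of the time against 1/8 and 16% to 96% against 1/5. The true default rate is unknown, and the denominator is unstated.

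The documents do not show that such a default exists, that Jewish and Muslim children's self-knowledge would be missed, or how many children lack a named second-question label. This is a better choice of reference for data already being collected, and it changes what an above-chance result may be taken to mean.

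**What to change.** 1. Fix the chance denominator in advance for each question (1/5 or 1/8; 1/7 or 1/10). Keep the option-count comparison as descriptive where a site has only one group.
2. For the US samples, base the conclusion on the association between the child's recorded affiliation and the label chosen. One suitable form is a permutation test of agreement across samples that preserves each label's overall selection rate. Support it with label-by-label selection rates in members and non-members, adjusted for age.
3. Include unaffiliated children given the same protocol version as a comparator. They answer the same items after hearing the same target label, which affiliation alone does not control for.
4. State that non-members who know their own status make the comparator rate too low, so a label-specific difference does not by itself prove self-knowledge within one sample.
5. Report I don't know separately. On the second question, score against named labels only for children whose Family Interest Form denomination is on the list, and report how many are not.

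Cost: additional analysis and a revised planned-analyses paragraph, with no new data. A between-sample comparison is somewhat less precise than a one-sample test. It also depends on the Jewish and Muslim samples, where the article reports recruitment difficulty, and it cannot be run at single-group sites.

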### Research question 3: How are religious and supernatural beliefs transmitted within and between generations?

Some of the data for this research question will come from comparing individual children to their parents/caregivers on the shared tasks described under Research Questions 1–2 (above). Beyond this, we include several tasks that tap into particular aspects of the various transmission processes that might shape children’s developing religious cognition and identity.

#### Justifications task: Assessing self-reported information sources for religious beliefs and behaviors

Building on previous work on children’s representations of supernatural phenomena, the Justifications task is designed to evaluate children’s understanding of their own “source knowledge” regarding the 2–3 religious agents featured in the Property Attributions task ([for similar tasks, see, e.g., 8, 38, 52, 53, 55, 84, 85]). This task is part of the Child Protocol; see Fig 2.

*Task design and procedure*. The Justifications task directly follows the Property Attributions task (described in an earlier section) and features the same set of agents included in that task—i.e., “normal, everyday people” as well 2–3 religious/supernatural agents (which we refer to in this manuscript as “Agent 1,” “Agent 2,” and, if applicable, “Agent 3”).

The task consists of a separate block of questions for each agent. Blocks are presented in a fixed order matching the order of presentation of agents in the Property Attributions task; as in that task, the first agent to be discussed is “people,” followed by Agent 1, Agent 2, and (if applicable) Agent 3.

Each block begins with a very brief introduction—“You just answered a lot of questions about [agent]”—followed by three open-ended questions presented in a fixed order: (1) “What else do you know about [agent]? You can tell me stories or any other things you know about [agent]”; (2) “Can you tell me more about how you know all of this about [agent]?”; and (3) “If you wanted to know more about [agent], how would you find out?”

The next set of questions within each block focuses in particular on children’s judgments about the reality status of the agent. First, the researcher asks the child to make a *reality judgment*: “Remember when we were talking about things that are real or not real? Can you remind me what you think about this: Is/are [agent] real or not real?” Then the researcher asks the child to assess their *certainty* about this reality judgment by asking, “How sure are you that [agent] is/are [child’s answer: real/not real]? A little bit sure, or really sure?” This is followed by an assessment of the child’s *source knowledge* regarding this reality judgment: “How do you know that [agent] is/are [child’s answer: real/not real]?” The final question in this set of questions is about the child’s sense of *community consensus* regarding this reality judgment: “Would most people in your [city/town/village] agree with you and say that [agent] is/are [child’s answer: real/not real]?”

Finally, the child is asked two additional questions designed to shed light on their construals of the agent: (1) a judgment about the *valence* of the agent, “Is/are [agent] good or bad?”; and (2) a judgment about the *corporeality* of the agent, “Does/Do [agent] have a body/bodies?” In contrast to other questions in the Child Protocol, researchers are encouraged *not* to press the child to make forced-choice responses to these questions; if a child gives a response like “in between” or “kind of,” the researcher instead asks, “Can you tell me more about that?”

In the US samples, this task is estimated to take 2 to 18 minutes with younger participants and 6 to 14 minutes with the oldest participants.

*Adaptation for US samples*. As described earlier, the final set of agents featured in the Property Attributions and Justifications tasks for the five religions included in US samples is presented in Table 2.

*Parallel tasks with parents/caregivers*. There is no parallel task for parents/caregivers.

*Planned analyses*. Before describing our analysis plans, we note that analyses of the many open-ended questions included in this task will require the development of coding schemes to note the presence and extent of various kinds of content (e.g., identifying certain content as “religious”; counting mentions of “God” or other religious agents; coding different types of explanations) as well as various manners of speaking (e.g., noting the use of generic sentences). In particular, we anticipate adapting the coding scheme developed by Harris et al. [49] and further expanded by Davoodi et al. [53] to characterize different types of explanations that children might give over the course of this task, including elaborations (e.g., of causal processes or properties of the agent), discussions of the source of their knowledge (e.g., references to learning about the agent in school, from a family member, from a religious text), and references to encounters with the agent (e.g., recounting first- or second-hand personal experiences with the religious agent).

First, we hypothesize that, for all open-ended questions, older children will offer richer and more detailed examples, descriptions, and explanations of what they know and how they know it [see 53, 54, 86]. To test this hypothesis, we will examine the main effects of participant age (4–10 years) using any relevant coding schemes we have developed to quantify and characterize children’s responses. We also anticipate examining the main effects of agent (people, Agent 1, Agent 2, and, if applicable, Agent 3), as well as statistical interactions between agent and participant age.

In terms of children’s perceptions of community consensus, we hypothesize that children will perceive stronger community consensus when asked about a normal, everyday person than when asked about the two or three supernatural/religious agents, and that this difference will increase with age [see 53, 87]. To test these hypotheses, we will examine the main effect of agent as well as statistical interactions between agent and participant age, considering the question about community consensus alone.

In terms of children’s source knowledge, we hypothesize that children will be more likely to name specific sources when asked about the two or three supernatural/religious agents than when asked about people; that mentions of specific sources will be inversely related to perceptions of community consensus (i.e., children will be more likely to name specific sources when discussing agents whose reality status they perceive to be controversial within their community); and that both of these effects will be exaggerated among older children [see 53]. To test these hypotheses, we will examine the main effect of agent, statistical interactions between agent and participant age, the main effect of community consensus, and statistical interactions between community consensus and participant age, considering the question about source knowledge alone.

Beyond these predictions, we plan to conduct exploratory analyses of all of the closed-ended questions that were not detailed in the current planned analyses; to compare responses across samples from different cultural-religious groups; to explore relationships between children’s responses in this task and information provided in the Parent Survey; and to examine relationships between this and other tasks included in the Child Protocol.

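### The Justifications consensus item measures agreement with the child's own real/not-real answer, but is read as community consensus without taking that answer into account

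*Protocol article*

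**What the plan says.** All of this is in the protocol article, Research question 3, Justifications task.

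- **The item** (Task design and procedure). For each agent the child gives a reality judgment, a certainty rating and a source for that judgment. The child is then asked "Would most people in your [city/town/village] agree with you and say that [agent] is/are", completed with the answer just given (real or not real).
- **First use, as outcome** (Planned analyses). The hypothesis is that "children will perceive stronger community consensus when asked about a normal, everyday person than when asked about the two or three supernatural/religious agents", with the difference growing with age. The test: "we will examine the main effect of agent as well as statistical interactions between agent and participant age, considering the question about community consensus alone".
- **Second use, as predictor** (Planned analyses). Naming specific sources is expected to be inversely related to perceived consensus, meaning that "children will be more likely to name specific sources when discussing agents whose reality status they perceive to be controversial within their community". The terms include "the main effect of community consensus, and statistical interactions between community consensus and participant age, considering the question about source knowledge alone".

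The child's own reality judgment for the agent is collected in the same block but is a listed term in neither analysis.

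Two other places matter. The introduction to the Property Attributions task tells children they may be asked about things they called not real. Only agents a child has not heard of are dropped from that task and from Justifications, so disbelievers stay in. The Sorting task's planned analyses predict that natural agents are called real more often than supernatural ones, increasingly so with age.

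**The concern.** The item and its interpretation refer to different things. The item asks whether others side with the child. The analysis text treats the reply as a statement about the community, namely whether it agrees within itself about the agent or finds the matter "agents whose reality status they perceive to be controversial within their community".

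The two coincide when the child believes and the community believes. They separate when the child disbelieves. A disbelieving child who sees a uniformly believing town perceives strong consensus, but must truthfully answer 'no'. That reply is the same as one from a child who sees the town split.

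This is unlikely to be random noise. Few children should call ordinary people not real, so the ambiguity falls mainly on the religious agents. The article itself expects reality judgments to diverge by agent type and age. That is the pattern the consensus hypothesis predicts: a lower value for religious agents, with a gap that widens with age. At stake are the agent effect, the agent-by-age interaction, the consensus-source association and the planned comparisons between samples. Each could partly express the child's own disbelief rather than a view of the community.

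**Working it through.** The article states no figure for this item, so there is none to reproduce. The check has two parts.

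**1. What each reply can mean**

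| Child's own answer | Child thinks the community is | Truthful reply | Does the child perceive consensus? |
|---|---|---|---|
| real | united on 'real' | yes | yes |
| real | divided | no | no |
| real | united on 'not real' | no | yes |
| not real | united on 'not real' | yes | yes |
| not real | divided | no | no |
| not real | united on 'real' | no | yes |

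A 'no' covers both perceived division and perceived unanimity against the child. Without the child's own answer, the reply does not even give the direction of the perceived majority.

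**2. Illustration of size (all rates assumed; none is in the article)**

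- q: share of children who think most local people say the agent is real, set equal for people and the religious agent and independent of own view.
- d: share of children who say the religious agent is not real; d = 0 for people.
- Agree rate = (1 − d)q + d(1 − q).
- Artefactual gap against people = q − agree rate = d(2q − 1).

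With q = 0.90, the agree rate for people is 0.90. For the religious agent:

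- d = 0.10: 0.90 × 0.90 + 0.10 × 0.10 = 0.82, a gap of 8 points
- d = 0.20: 0.80 × 0.90 + 0.20 × 0.10 = 0.74, a gap of 16 points
- d = 0.30: 0.70 × 0.90 + 0.30 × 0.10 = 0.66, a gap of 24 points

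Perceived community belief is 90% in every case. At d = 0.10, 0.20 and 0.30 the gaps are 6, 12 and 18 points for q = 0.80, and 10, 20 and 30 points for q = 1.00.

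*Age.* If disbelief were 10% at one age and 30% at another, with q fixed at 0.90, the gap would change from 8 to 24 points. That is a 16-point agent-by-age effect with no change in perceived community belief.

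*Relaxing independence.* Let q be only the share of disbelievers who think most people say 'real'. The difference between perceived majority belief and the agree rate is still d(2q − 1). At d = 0.30 it is 24 points for q = 0.90, 12 for q = 0.70 and 0 for q = 0.50.

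*Detectability.* Take the planned US minimum of 75 children per sample, a two-sided 5% test and the two agents treated as independent samples (an approximation, since the data are within-child). With q = 0.90, an agent effect would be declared about 29%, 73% and 95% of the time at 10%, 20% and 30% disbelief.

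**Effect of conditioning.** Among children who call the agent real, d = 0 for both agents, so both agree rates equal q and the gap in this illustration is 0.

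**The case against.** The strongest reply is that the item is sound for what the task description says it measures: the child's sense of consensus about that particular judgment. A disbeliever in a believing town correctly reports that others do not share the view, and may well feel the matter is contested, which is close to what the source hypothesis needs. The protocol also calls itself mostly exploratory, presents these as basic analyses, and collects the variable needed for adjustment. This stands as far as the item goes. It does not rescue the planned analyses, which move from agreement with the child to consensus or controversy in the community. The general promise of exploratory work on closed-ended questions not already detailed does not commit to any correction for this one.

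Several stronger readings are tempting but unsupported:

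- *That the plan forbids adjustment.* A reader might infer this from "considering the question about community consensus alone". The parallel phrase for source knowledge is used while consensus serves as a predictor, so 'alone' names the outcome and does not bar covariates.
- *That such a child is scored as perceiving no consensus.* No scoring is printed. The fault lies in the stated interpretation and listed terms.
- *That a bias of a given size is expected.* The article gives neither disbelief rates nor perceived community belief. The featured agents include the setting's main god and other prominent figures, and unfamiliar agents are dropped, which points to low disbelief among affiliated children.
- *That the distortion is known to be worst in unaffiliated or minority-faith samples.* Higher disbelief among unaffiliated children is plausible, but no rates are given. In a minority faith the likelier case may be a believing child in a disbelieving community.
- *That recoding to a perceived majority view repairs the analysis.* It gives direction, whereas the hypothesis concerns strength. It also miscodes every child whose 'no' means a divided community.

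**Conclusion.** The point holds as a mismatch between the item and the interpretation built into its analysis. The stated analyses can produce the hypothesised agent and agent-by-age effects, and distort the consensus-source association, partly through the child's own disbelief. How far they do so cannot be determined from the article. The 8, 16 and 24 points are illustrations resting on 90% perceived community belief, independence from the child's own view, and disbelief of 10%, 20% and 30%. The effect shrinks as children project their own view onto others, and is small where nearly all children call the agent real. The link to the Sorting prediction is indirect, since that prediction concerns natural agents rather than ordinary people. This is not merely detail left to a fuller plan, because the item wording and the way its answers are to be read are both stated and do not match.

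**What to change.** In the planned analyses of the Justifications task:

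1. **Consensus as outcome.** Stratify by, or adjust for, the child's own reality judgment for that agent. For example, make the comparison of people with religious agents, and its interaction with age, primarily among 'real' judgments, and report 'not real' judgments separately. Stratifying is easier to interpret than adjusting, because few children are likely to call people not real and that stratum would hold almost only religious agents.
2. **Consensus as predictor.** Add the child's reality judgment for the agent to the source-mention model.
3. **Wording.** Describe the item as perceived agreement with the child's own judgment wherever it is now called community consensus or taken to show controversy.
4. **Secondary description only.** A derived perceived majority view may be reported, with the stated limit that a 'no' cannot separate a divided community from one united against the child. Only a differently worded item could separate them.

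The cost is smaller strata, hence less precision, and a little more analysis work. No new data are needed, since the reality judgment is already collected in the same block.
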